### Objectives of the evaluation

This evaluation study entails an effect, process and cost evaluation of offered geriatric health care and has four main objectives. First of all, the study aims to determine to what extent the program, in comparison with other usual forms of geriatric care, leads to a retention in functioning and quality of life of at risk elderly, a reduction in the burden of care for the patient's primary informal caregiver, shorter lengths of hospital stay, and a reduction of 'wrong bed' problems as well as (re-) admission to hospitals, nursing homes and mortality. In addition, it will show the extent to which program care including a stay at a reactivation centre, leads to better functioning and quality of life of elderly patients in need of complex care. Secondly, the study aims to determine to what extent the triage instruments used in the program detect increased risk for functional loss and to determine how criteria for triage should be adjusted to optimally link the offered interventions to the needs of the individual elderly at risk. Thirdly, the evaluation will determine to what extent the program, in comparison with other, usual forms of geriatric care in the Netherlands, leads to a better structure and process of care. Finally, the cost-effectiveness of the program (both including and excluding a stay at a reactivation centre) will be determined in comparison with other usual forms of geriatric hospital care in the Netherlands.

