### Pilot study

A pilot study was conducted in the intervention hospital (Vlietland hospital) to choose the best triage instruments to identify elderly patients eligible for the reactivation program. Furthermore, the pilot results will be used to identify possible practical implementation problems in preparation for the main evaluation study and serve as base for power calculations for the main study. In the pilot study, all patients (65 years or older) who were admitted to the Vlietland hospital between June 2010 and October 2010, were asked to participate. Around 500 patients and 200 informal caregivers were included at baseline (within 48 hours after hospital admission) and of this group around 300 patients and 160 informal caregivers completed questionnaires at the 3-month follow up (see figure 1: Flow chart pilot study). Follow up measurements at twelve months after hospital admission will be finalized in November/December 2011.

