### Participants

#### Population

The target population of the study consists of elderly persons (65 years and older) who are at risk for functional loss and are admitted to one of the three hospitals for at least two days. All patients will receive the usual care offered by each of the hospitals. All relevant hospital departments will be included in the study and admission may be elective or acute. Figures 2 and 3 (flowcharts) provide an overview of the flow of patients in the study. Through a first triage step, all patients at risk for functional loss will be identified with the ISAR-HP [46,47]. These at risk patients will be eligible to receive the hospital based reactivation care program and therefore will be asked to participate in the study. In the Vlietland hospital, an additional triage will take place using the short Neuropsychiatric Inventory [48,49] and the Mini Mental State Examination [50] to identify elderly patients eligible for a stay at the reactivation centre. This group will then be randomised to program care including a stay at the centre (n = 200) or program care excluding a stay at the centre (n = 200). The primary informal caregivers of the participating patients will be asked to answer several questions about the patient in a telephone interview as well as fill out mailed paper questionnaires on quality of life, burden of care and other outcomes at time of hospital admission of the patient, three months after hospital admission and twelve months after hospital admission. Furthermore, health care professionals from each participating hospital will be asked to complete a survey on processes of health care.

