#### Inclusion criteria

• patients aged 65 years or older

• admitted in one of the participating hospitals and staying >48 hours

• at risk for functional loss (ISAR HP ≥ 1)

Additional criteria for a stay at the centre for prevention and recovery

• ISAR HP ≥ 2 and/or MMSE ≤ 27 and/or NPI ≥ 3

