#### Demographics and triage (table 1)

##### Triage: identification of elderly at risk for functional loss

Triage data is gathered within 48 hours of hospital admission in order to identify elderly at risk for functional loss at an early stage. Based on the pilot results the Identification of Seniors At Risk-hospitalized patients (ISAR-HP) is chosen as the main triage instrument in order to achieve information on a combination of factors that have shown to be important in predicting functional loss. The ISAR HP questionnaire is administered to the patient and consists of four questions on education and need of help with travelling, walking or help with housekeeping in the period before admission to the hospital [46]. A person is considered at risk for functional loss and is therefore eligible for treatment with the program if he/she scores one or higher on the ISAR HP. This is a different score from the originally set cut off score of 2 or higher as is stated in the paper written by Buurman et al (2010), and can be explained by the differences in characteristics and diagnoses of the studied population. In addition, the NPI-Q and MMSE are administered in order to identify elderly who are eligible for an additional stay at the centre for prevention and reactivation as part of the program. Patients will be considered eligible for a stay at the reactivation centre when they score 2 or higher on the ISAR HP and/or 3 or higher on the NPI-Q and/or 27 or lower on the MMSE. The Neuropsychiatric index (NPI-Q) is the validated short version of the NPI [49]. It aims to identify neuropsychiatric symptoms present in the patient in the last month by means of twelve symptoms (e.g. delusions, aggression, hallucinations) and also measures the emotional burden for the caregiver. The NPI is administered to the primary informal caregiver of the patient by means of a telephone interview at time of hospital admission. The Mini Mental State Examination (MMSE) measures cognitive functioning by means of interviewing the patient using questions on orientation in time and space, short-term and middle-term memory, comprehension and other cognitive dimensions [50,52].

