### Data analysis

#### Triage

Data will be gathered on risk factors for functional decline and predictive models for functional decline at 3 and 12 months can be developed using multivariate regression techniques and data from control settings. The quality of the predictive models will be assessed by explained variance for continuous outcome measures and by ROC-curves for dichotomous outcome measures. The quality of the model that fits the program eligibility criteria will be compared to models with other risk factors involved and/or other cut-off points on the triage instruments. This way the added value of another triage method can be objectively assessed. These analyses were already partly done using preliminary pilot study results but will be repeated using final results of the main evaluation study. Furthermore, main study results will be used to evaluate the validity of the model(s) with internal validation techniques (bootstrapping) and cross validation between the three settings whereby each setting acts as a test-population for model(s) developed in the other settings [81].

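### The main cohort admits only patients scoring ISAR-HP ≥ 1, so it cannot show how accurately that threshold detects risk, or what a criterion reaching score-0 patients would add

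*Protocol article*

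**What the plan says.** All references are to the protocol article.

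- **Programme threshold** (Triage, under Demographics and triage): a patient is "eligible for treatment with the program if he/she scores one or higher on the ISAR HP". The instrument's own cut-off was higher: "This is a different score from the originally set cut off score of 2 or higher".
- **Study entry** (Inclusion criteria): patients must be "at risk for functional loss (ISAR HP ≥ 1". The Population section adds: "These at risk patients will be eligible to receive the hospital based reactivation care program and therefore will be asked to participate in the study". This covers all three hospitals. The text describes no follow-up of patients scoring 0.
- **Objective** (Objectives of the evaluation): the study is to "determine to what extent the triage instruments used in the program detect increased risk for functional loss", and to say how the criteria should be adjusted.
- **Analysis** (Data analysis, Triage): "The quality of the model that fits the program eligibility criteria will be compared to models with other risk factors involved", and also to models with other cut-offs. The measures are explained variance and ROC curves. Part of this was done on preliminary pilot results, and it is to be repeated on the main study. Development is said to use control-setting data, but in the cross-validation "each setting acts as a test-population for model(s) developed in the other settings".
- **Pilot** (Pilot study): "all patients (65 years or older) who were admitted to the Vlietland hospital between June 2010 and October 2010, were asked to participate". About 500 patients were included at baseline and about 300 completed three months. The Strengths section says the pilot came before the programme was implemented.
- **Centre criteria** (Inclusion criteria): ISAR-HP ≥ 2, MMSE ≤ 27 or NPI ≥ 3, alone or in combination.

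**The concern.** A detection rule can be judged only if some patients who fail it are also followed. Here the rule under evaluation decides who enters the cohort. Patients scoring 0 who go on to decline are never seen, and neither are those scoring 0 who stay well. Sensitivity, specificity and negative predictive value (NPV) of ISAR-HP ≥ 1 all need these patients.

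The threshold was lowered from 2 to 1, and the paper presents clear eligibility criteria as one of its contributions. Whether ≥ 1 still misses patients who decline is a natural question for the second objective, and the main cohort is silent on it. If the eligibility model were coded as the bare ≥ 1 indicator, any informative rival would beat it, and that result would say nothing about the threshold.

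A second, smaller difficulty lies in the same section. Three-way cross-validation makes the intervention hospital both a development and a test setting, although the programme there is meant to prevent the outcome being predicted.

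**Working it through.** **1. The plan's own figures.** The article gives no figure for the triage analysis. Its only power figures concern the hospital comparison. With a two-sided 5% level (assumed; the article states none), 733 v 300 at d = 0.25, 733 v 300 at d = 0.2 and 733 v 600 at d = 0.2 give 95.4%, 83.1% and 95.3%, against the stated 95%, 83% and 95%. They reproduce and do not bear on this point.

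**2. What follows by definition.** Let D be decline and S the ISAR-HP score. In a cohort with S ≥ 1 for everyone:

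- sensitivity of ≥ 1 = P(S ≥ 1 | D) = 1
- specificity of ≥ 1 = P(S = 0 | no D) = 0
- AUC of the indicator = (sensitivity + specificity)/2 = 0.50; explained variance = 0
- NPV = P(no D | S = 0): undefined, as nobody has S = 0

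Bootstrapping, or cross-validation between three settings with the same restriction, leaves these values unchanged.

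**3. Illustration.** The article gives no score distribution or risks by score, so these are assumptions: 35% of admissions score 0 with decline risk 10%. The other 65% split 40:30:30 over scores 1, 2 and 3+, with risks 25%, 35% and 50%.

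| Score | Share | Decline | No decline |
|---|---|---|---|
| 0 | 0.350 | 0.03500 | 0.31500 |
| 1 | 0.260 | 0.06500 | 0.19500 |
| 2 | 0.195 | 0.06825 | 0.12675 |
| 3+ | 0.195 | 0.09750 | 0.09750 |
| All | 1.000 | 0.26575 | 0.73425 |
| ≥ 1 | 0.650 | 0.23075 | 0.41925 |

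| Quantity | All admissions | Main cohort (≥ 1 only) |
|---|---|---|
| Sensitivity, ≥ 1 | 0.23075/0.26575 = 86.8% | 100% |
| Specificity, ≥ 1 | 0.31500/0.73425 = 42.9% | 0% |
| PPV, ≥ 1 | 0.23075/0.650 = 35.5% | 35.5% |
| Sensitivity, ≥ 2 | 0.16575/0.26575 = 62.4% | 0.16575/0.23075 = 71.8% |
| Specificity, ≥ 2 | 0.51000/0.73425 = 69.5% | 0.19500/0.41925 = 46.5% |
| PPV, ≥ 2 | 0.16575/0.390 = 42.5% | 42.5% |
| AUC of the score | 0.71 | 0.62 |

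**4. Range.** Let the score-0 share run over 20%, 35% and 50%, and the score-0 risk over 5%, 10% and 20%. In all admissions, ≥ 1 then has sensitivity 64–97% and specificity 24–60%; ≥ 2 has 46–69% and 59–78%; the score AUC is 0.63–0.78. The main cohort returns the same values in all nine scenarios: 100% and 0% for ≥ 1, 72% and 47% for ≥ 2, and AUC 0.62.

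**5. What survives the restriction.** Risk at each score from 1 upward and both PPVs are unaffected. Ratios between cut-offs also survive: sensitivity at ≥ 2 within the cohort equals population sensitivity at ≥ 2 divided by that at ≥ 1 (0.624/0.868 = 0.72). The centre criteria vary among patients scoring ≥ 1, so MMSE, NPI and other factors can be compared there.

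**The case against.** A reader might infer that the second objective cannot be met at all, that no change of cut-off can be studied, or that the analysis must favour replacing the ISAR-HP. The article does not support these readings.

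- Score-1 patients are enrolled and followed, so a move back up to the original cut-off of 2 can be examined through the risk at score 1 and the PPV at ≥ 2.
- The objective speaks of instruments in the plural. The centre's ISAR-HP, MMSE and NPI thresholds are part of triage and vary within the cohort.
- The article does not say that the eligibility model is the bare ≥ 1 indicator. A model with the graded score and the centre criteria is not constant; in the illustration the score keeps an AUC of 0.62. That a rival wins automatically is true only of the bare indicator.
- The pilot was not restricted by ISAR-HP, was run partly to choose the triage instruments, and has already been used for part of these analyses.

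On cross-validation, a reader might infer that poor performance in the intervention hospital could never be told apart from a programme effect. That is too strong. A fairly uniform benefit would mainly shift calibration rather than ranking, and the control hospitals give a benchmark.

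All of this stands. It narrows the point without removing it: the analysis is to be repeated on main-study data with no statement that the accuracy of the ≥ 1 threshold is out of reach there.

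**Conclusion.** The point holds in a limited form. The main cohort cannot estimate the sensitivity, specificity, NPV or AUC of ISAR-HP ≥ 1, or the effect of any criterion that would admit score-0 patients. That part of the second objective cannot be answered by repeating the comparison on main-study data. Sensitivity, specificity and AUC for higher cut-offs can be computed within the cohort, but they are not population values.

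The 100%, 0% and 0.50 for the ≥ 1 indicator are exact and need no assumption beyond the entry rule. The other accuracy figures rest on assumed score shares and risks. The conclusion also assumes that no score-0 patients are followed. The text describes none, but the flow charts were not available to check.

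The consequence is confined to the triage objective, one of four. The hospital comparison, the nested trial and the cost-utility analysis are untouched. Nothing here says which threshold the programme should use.

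**What to change.** Amend the triage part of the data analysis section in three ways.

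1. **Assess the ≥ 1 threshold on the pilot.** Report its sensitivity, specificity, NPV and AUC against rival criteria there, with bootstrap correction for optimism because the instrument was chosen on those data.
2. **Limit the main-study triage analysis to patients scoring ≥ 1.** State that it grades risk among them (by score, cut-offs from 2 upward, MMSE, NPI, other factors), and that within-cohort sensitivity, specificity and AUC are not population values. Narrow the second objective to match.
3. **Reconcile the two statements about settings.** Develop and cross-validate models in the control hospitals and the pilot. Report performance in the intervention hospital separately, with calibration, since a programme effect can shift it.

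The cost is re-analysis of existing data and wording. The downside is precision, and reliance on one hospital with about 300 of 500 patients seen at three months. Under the central assumptions, 300 × 0.26575 ≈ 80 decline and 220 do not. The 95% half-widths (normal approximation) are 1.96 × √(0.868 × 0.132/80) ≈ 7 percentage points for sensitivity and 1.96 × √(0.429 × 0.571/220) ≈ 7 points for specificity, before the optimism correction.

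If more is wanted, a sample of score-0 patients in the control hospitals could be enrolled and followed, at the price of extra consent and interviews.

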### Description of the hospital based reactivation care program

The program is developed to prevent and/or reduce hospital related functional loss among at risk elderly by offering an individualized treatment plan that is based on problem-solving principles. It includes interventions that are integrated, multidisciplinary and goal-oriented at physical, social, and psychological domains of functional loss and combines existing treatment methods and routes for reactivating at risk elderly persons into an individual care package.

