### Strengths

First of all, this study uses a mixed methods design of quantitative and qualitative measures that provide information on three elements as stated by Donabedian [87]: structural issues (e.g. materials, personnel, organization and coordination of care), processes (e.g. activities of professional in diagnosing and treating the patient) and patient and caregiver outcomes such as physical functioning and quality of life. According to Donabedian, the combination of these elements allows for better interpretation of findings, as one method may strengthen interpretation in cases where another method cannot explain variances or outcomes. Qualitative data may generate further hypotheses that may be explained by quantitative process and outcome data. It can also provide a context within which outcomes can be explained more in-depth. Secondly, a pilot study was conducted at the intervention hospital before implementing the program, which optimised beforehand the triage for selecting patients to be included in the main study as well as the power calculations and the practical implementation of the main study. Several practical and implementation problems were encountered in the pilot study (e.g. logistics within hospital, personal communication with hospital personnel etc), making it possible to prevent similar problems and sources of bias when conducting the main study. Within the cohort study, dynamic randomisation will be implemented in order to prevent extra bias and missing data per questionnaire. Furthermore, loss to follow up will be minimized by conducting personal interviews through house calls at three months and 12 months after hospital admission. Finally, the evaluation will be conducting a cost-effectiveness study, which will improve/increase current knowledge on the feasibility of implementing transition programs such as the one evaluated here.

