### Weaknesses

This study is mainly a cohort study and not a randomised controlled trial (except for the evaluation of a stay at the centre for prevention and reactivation). Nevertheless a cohort study seems our best option for several reasons: Firstly, during hospital treatment, contamination of a control group would be inevitable within one hospital since the same personnel will be treating patients from different groups at the same departments [88]. Secondly, the new program will be the standard care provided in the intervention hospital thereby making randomisation within the hospital not possible. Furthermore, randomisation of treatments between hospitals is not possible since each hospital already has its own standard provided care. Thirdly, during the follow up period after hospital discharge people already have their own regular general practitioner (GP) whose practice is usually close to the patient's home and who is familiar with the patients health and history, making it unrealistic to randomize patients among GP's [88] or home care organizations as well as other first line practitioners. Finally, by conducting a prospective cohort study we aim to investigate health care as provided in a real life situation, thereby improving the generalisability of the study.

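### The triage models are described as control-based, yet their three-way cross-validation rotates in the intervention hospital with no allowance for the programme meant to prevent the predicted outcome

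*Protocol article*

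**What the plan says.** The second objective in the Protocol article (Objectives of the evaluation) is "to determine to what extent the triage instruments used in the program detect increased risk for functional loss", and to find out how the triage criteria should be adjusted.

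Under Data analysis, Triage, the article first states that "predictive models for functional decline at 3 and 12 months can be developed using multivariate regression techniques and data from control settings". Model quality is to be "assessed by explained variance for continuous outcome measures and by ROC-curves for dichotomous outcome measures". Calibration is not named. The same paragraph then adds bootstrapping and "cross validation between the three settings whereby each setting acts as a test-population for model(s) developed in the other settings".

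On the intervention itself, the programme description says: "The program is developed to prevent and/or reduce hospital related functional loss among at risk elderly". The Weaknesses section says that "the new program will be the standard care provided in the intervention hospital thereby making randomisation within the hospital not possible". Power calculation and effect size likewise counts all 1100 intervention-hospital patients as treated with the programme. The Randomisation section says otherwise: more patients will be eligible than can be treated, and dynamic randomisation decides who receives the programme.

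**The concern.** A triage rule has to identify patients who will decline if they do not get the extra care. The sentence on development data respects this by pointing to control hospitals. The cross-validation sentence does not. The intervention hospital becomes a source of development data for the models tested in each control hospital, and the test population for the model built in the two control hospitals. Outcomes there reflect risk under the programme.

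If the programme works, poor agreement between predicted and observed decline could mean a weak model, a model that does not transport between hospitals, or an effective programme. The planned validation cannot separate these, because the Triage section includes no term for programme exposure. What is at stake is the validation evidence for the second objective. The comparison of effects between hospitals is not touched.

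**Working it through.** **1. The rotation.** Call the control hospitals A and B and the intervention hospital I.

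| Test set | Development set | Programme patients enter |
|---|---|---|
| A | B + I | development |
| B | A + I | development |
| I | A + B | test |

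No rotation is free of the programme. If the earlier sentence is read strictly, so that only control hospitals develop models, I still remains a test set.

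**2. Share of the mixed development sets.** Inputs are from Power calculation and effect size: 1100 in I, at least 500 to 600 in each control hospital, and 733 and around 300 analysable at three months.
- Baseline: 1100/(1100+500) = 69%; 1100/(1100+600) = 65%.
- Analysable: 733/(733+300) = 71%, if the other control hospital yields 300.
- If that hospital reached the preferred 900 (600 analysable): 1100/2000 = 55% and 733/1333 = 55%.

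**3. Effect size.** The article gives no figure for the triage validation, so I take its planning effects. Its stated powers reproduce (two-sided 5% assumed): 95.4% against 95% (300 v 733, d = 0.25), 83.1% against 83% (300 v 733, d = 0.2) and 95.3% against 95% (600 v 733, d = 0.2).

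**4. Shift in predicted risk, uniform effect.** Assumptions not in the article: 35% decline at follow-up under usual care, d converted to an odds ratio by exp(d × π/√3), equal case mix, and every patient in I exposed.
- d = 0.25: OR = exp(0.25 × 1.814) = 1.57. Usual-care odds 0.35/0.65 = 0.538; 0.538/1.57 = 0.343; risk under the programme 25.5%.
- Mixed model: 0.69 × 25.5 + 0.31 × 35 = 28.4%, tested where 35% occurs.
- Control-based model in I: 35 − 25.5 = 9.5 points too high.

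Range by the same formulas:

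| Usual-care risk | d | Exposed in I | Mean risk in I | Mixed model predicts | Over-prediction in I |
|---|---|---|---|---|---|
| 35% | 0.25 | 100% | 25.5% | 28.4% | 9.5 |
| 35% | 0.20 | 100% | 27.3% | 29.7% | 7.7 |
| 35% | 0.25 | 50% | 30.3% | 31.7% | 4.7 |
| 65% | 0.25 | 100% | 54.1% | 57.5% | 10.9 |

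The 35% and 65% are the Background's figures for loss at discharge in 70-year-olds and in those aged 90 or older. They are borrowed here only to span a range.

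**5. The measures the plan names.** A large-sample logistic simulation used one risk score with log-odds slope 1.0, about 36% decline under usual care and d = 0.25. In the last two columns the first figure is predicted and the second observed.

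| Effect | Exposed in I | Slope, I + B model | I + B model in A | A + B model in I | AUC of A + B model in I |
|---|---|---|---|---|---|
| None (d = 0) | – | 1.01 | 36.0 v 35.8% | 36.0 v 35.8% | 0.74 |
| Uniform | 100% | 1.00 | 30.0 v 35.5% | 35.8 v 27.7% | 0.74 |
| Uniform | 50% | 1.00 | 33.3 v 36.0% | 36.2 v 32.1% | 0.74 |
| Larger at high risk (slope −0.4) | 100% | 0.72 | 28.5 v 35.3% | 35.6 v 25.7% | 0.66 |
| Larger at high risk (slope −0.4) | 50% | 0.86 | 32.2 v 35.6% | 35.8 v 30.7% | 0.70 |

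A uniform effect moves the level of predicted risk and leaves ranking intact. An effect that grows with risk also flattens the predictor-outcome relation, which lowers AUC in the intervention hospital and, by the same mechanism, explained variance. The size of the flattening (0.4) is an assumption.

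**The case against.** The strongest reply is that the models are stated to be developed on control data and that the rotation only evaluates them. That stands as far as it goes. A reader might infer that the final triage models no longer predict the course without the programme, but nothing in the article says they are fitted to intervention-hospital patients. What is affected is the validation.

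Other inferences go further than the text:
- **Cut-offs biased by programme patients.** The comparison of cut-off points is described before the cross-validation, and nothing ties it to the rotated models.
- **Every at-risk patient in the intervention hospital is exposed.** Power calculation and Weaknesses suggest so; Randomisation says otherwise.
- **Control patients are untreated.** They receive usual care, including care-hotel replacement care and, in one hospital, coordinated discharge (Setting).
- **Selection by triage score sets the intervention hospital apart.** ISAR-HP ≥ 1 is required in all three hospitals.
- **The better the programme works, the worse its triage must look.** Under a uniform effect the AUC, which underlies the ROC analysis that the plan names, barely changes.

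Two further points have some weight. The second objective also asks how to link interventions to individual needs, for which data from the hospital offering them are useful. And the effect analysis plans an interaction between hospital type and risk group, which would show whether the programme changes the relation between risk and outcome. That interaction is not part of the validation, however, so it does not repair it.

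Against the reply, an effect that rises with risk is plausible here. Eligibility for the extra-intensive centre stay depends on ISAR-HP, MMSE and NPI, the instruments under evaluation.

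**Conclusion.** The point holds for the cross-validation. The Triage section names control settings for development and then prescribes a rotation in which the intervention hospital makes up most of two development sets and is the third test set, with no allowance for programme exposure. This is a stated rule, not a detail left to a later document.

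With 35% usual-care decline, d = 0.25 and full exposure, mixed models predict about 28% against 35% in a control hospital. A control-based model over-predicts by roughly 9 points in the intervention hospital (9.5 by direct arithmetic, 8.1 in the simulation). Half exposure roughly halves this, and with no programme effect it is zero. Loss of AUC, to about 0.66 in the example, requires an effect concentrated in high-risk patients. The change is worth making because a main objective depends on the validation, but the conclusion does not extend to the control-developed models themselves or to the choice of cut-offs.

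**What to change.** 1. For risk under usual care, develop and cross-validate between the two control hospitals only (develop in one, test in the other, and the reverse), with bootstrapping in the pooled controls.
2. Report the intervention hospital separately, labelled as performance under the programme. Alternatively, include it only in a model with a programme-exposure term and programme-by-predictor interactions.
3. Reconcile the Randomisation section with Power calculation and Weaknesses on who in the intervention hospital receives the programme, since any exposure term depends on it.
4. The pilot may serve as a supplementary check, because "a pilot study was conducted at the intervention hospital before implementing the program". Restrict it to ISAR-HP ≥ 1, as it invited all patients aged 65 or older, so fewer than its roughly 300 three-month responders may qualify. State that it was used to choose the triage instruments and is not an independent test of them.

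The change is to analysis wording and needs no new data. The cost is a smaller development and validation sample: about 2 × 300 = 600 analysable controls if each control hospital enrols the minimum of 500 and yields 300.
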